### Qualitative Interviews

A conventional inductive content analysis approach will be used [36]. Data will be systematically examined. Codes and themes will be generated based on the content, with no reliance on preconceived theories. Weekly meetings will be held with the research team and analyst to examine themes, validate the coding process, and maintain consistency and depth in data interpretation.

### Ethical Considerations

This study gained Hamilton Integrated Research Ethics Board approval on November 21, 2022 (project #14096) and was registered on ClinicalTrials.gov (identifier NCT05114187). Participants were required to provide informed consent and were informed of the length of time of the e-learning, surveys, and email campaign; they were also informed about the details surrounding data collection, storage, and investigator identities. Participants’ identities and confidentiality were maintained throughout the research study. All participant data were deidentified and all findings will be nonidentifiable. There is no known risk or harm to participating in this study or publicizing its results or findings. Participants in run 1 were provided with a CAD $40 (US $28.6) Amazon gift card, and participants in run 2 were provided with AskingCanadians points that can be redeemed for various gift cards as compensation for participation in the study.

## Results

### Initial Cohort Participants

Recruitment began on September 6, 2022, and finished on October 2, 2022. A total of 125 participants were randomly assigned to the intervention (n=61) or control (n=64) group, and data collection concluded in January 2023 (Figure 2).

**Figure 2 figure2:**
[figure not shown]
Study flow diagram for run 1.

Preliminary results showed a substantial number of participants who did not engage with the protocol as initially intended. A number of participants were identified as not having completed the protocol as intended, as demonstrated by “fast-tracking” through the e-learning (ie, clicking next without allowing time for reading or listening to content) or by repeatedly clicking “I don’t know” on prestudy or poststudy surveys.

Following this, a decision was made to recruit an additional cohort of participants (n=100) using learnings gained from the initial recruitment cohort concerns. A paid panel service, AskingCanadians, was engaged to assist with recruitment. AskingCanadians is a reputable paid panel service that was able to specifically target family and friend care partners of people living with dementia.

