**Results:**

Initial recruitment began on September 6, 2022, and concluded on October 2, 2022. A total of 125 participants were randomly assigned to the intervention (n=61) or control (n=64) group. Data collection concluded in January 2023. Preliminary feasibility results showed a substantial number of participants who did not engage with the protocol as intended. A decision was made to recruit a second cohort of participants to address these protocol deviations. Secondary recruitment began on June 12, 2023, and concluded on June 27, 2023. A total of 100 participants were randomly assigned to the intervention (n=53) or control (n=47) group. Data collection concluded in September 2023. Further results will be published in peer-reviewed journals and presented at conferences.

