### Clinical Effectiveness Outcomes

#### Knowledge

Knowledge will be measured through the Dementia Knowledge Assessment Scale (DKAS; reliability α=.85; ωh=.87; overall scale) [29]. The DKAS consists of 25 items on different aspects of dementia that could be answered with “True,” “Probably True,” “False,” “Probably False,” or “I don’t know.”

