### Knowledge, Self-Efficacy, and Burden

Linear mixed models will be used to assess the relationship between group assignment and score for each of the outcomes: the DKAS and its subdomains (causes and characteristics, communication and behavior, care considerations, and risks and health promotion), the RSCSE and its subdomains (obtaining respite, managing disruptive behaviors, and controlling upsetting thoughts), and the ZBI. All models will include the 2 stratification factors, education level (high school equivalent or less, some college or university, and college or university or graduate degree) and care partner type (care partner to a spouse, care partner to a parent, and care partner to someone other than a spouse or parent). Group assignment will be included as the primary independent variable of interest with interaction from time to determine how the relationship between outcome score and group assignment will change from baseline to follow-up. Potential effect modifiers, including age (categorized as <44 years, 45-64, and ≥65 years), gender, education level, stage of dementia (mild [early-stage] dementia, moderate [middle-stage] dementia, severe [late-stage] dementia, or “I don’t know”), and length of time as a care partner (less than 3 months, more than 3 months but less than 1 year, more than 1 year but less than 2 years, more than 2 years but less than 5 years, or more than 5 years), will be explored in relation to group assignment. These variables will be retained in the model if the likelihood ratio test indicates a significant difference between the nested model and the full model (*P*<.05). If they are not significant modifiers of the group-outcome relationship, then they will be investigated as effect modifiers with respect to time. An intention-to-treat analysis will also be performed and include all individuals as per group assignment. A per-protocol analysis will also be performed. Correlations between the number of lessons in the intervention completed and the DKAS score will be analyzed.

We will also look for inverse correlations between the DKAS and ZBI scores, as well as between the RSCSE and ZBI scores. Analyses will be performed using an α level of .05 and 2-sided tests. All analyses will be conducted using RStudio software (Posit).

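### Repeated don't-know answers, a valid response on the knowledge scale, are counted as a protocol deviation; the per-protocol set should be stated not to depend on them

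*Protocol article*

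**What the plan says.** - Results, Initial Cohort Participants: "A number of participants were identified as not having completed the protocol as intended". Two alternative signs are given: clicking through the e-learning without time to read or listen, or "by repeatedly clicking “I don’t know” on prestudy or poststudy surveys". They are joined by *or*, so survey answers alone are enough.
- Abstract, Results, on the same problem: "A decision was made to recruit a second cohort of participants to address these protocol deviations".
- Clinical Effectiveness Outcomes, Knowledge: "Knowledge will be measured through the Dementia Knowledge Assessment Scale". Its 25 items "could be answered with “True,” “Probably True,” “False,” “Probably False,” or “I don’t know".
- Data Analysis, Knowledge, Self-Efficacy, and Burden: "A per-protocol analysis will also be performed". The set is not defined there. The same paragraph plans an intention-to-treat analysis of everyone as assigned, and adds: "Correlations between the number of lessons in the intervention completed and the DKAS score will be analyzed".
- Poststudy Surveys: these open at T2, 8 weeks after the start and so after exposure to the lessons.
- e-Learning Content and Table 1: the intervention arm has 10 lessons and the control arm has 1.

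**The concern.** A response option that the knowledge instrument itself offers is also read as evidence of not following the protocol. The Abstract notes that care partners may know little about dementia, so some genuine participants will use that option often, and they will be low scorers.

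If the per-protocol set is built on this description, membership depends partly on the T2 knowledge answers. That is selection on the outcome after randomization. Effective lessons reduce don't-know answers, so the control arm loses more of its low scorers and the arms look more alike than they are. The knowledge estimate is meant to inform a larger trial, so a diluted per-protocol figure could mislead its planning.

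Two related points concern exposure. A fast-tracking rule applied lesson by lesson gives the intervention arm ten chances of being flagged and the control arm one. A lesson that was clicked through can also count as completed in the planned correlation with the DKAS score.

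**Working it through.** No figure in the article depends on this point, so there is none to reproduce. The check has four steps.

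**1. The passages side by side.** Results makes repeated don't-know answers sufficient for non-adherence; the Abstract calls the problem protocol deviations; Knowledge offers the same answer as valid; Data Analysis plans a per-protocol set. No passage connects the flag to that set. The link is an inference from its being the only account of not following the protocol.

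**2. Upper bound: a sharp cut on the T2 score.** Assumptions: T2 score normal with SD 1, control mean 0, intervention mean 0.5, and everyone below c removed. The fraction removed is Φ(c − μ). The retained mean is μ + φ(c − μ)/[1 − Φ(c − μ)].
- c = −1: removed 15.9% of controls and 6.7% of intervention. Means 0.288 and 0.639; difference 0.351, and 0.351/0.5 − 1 = −30%.
- c = −1.5: removed 6.7% and 2.3%. Means 0.139 and 0.555; difference 0.416, or −17%.

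This treats the don't-know count as a perfect marker of the T2 score and compares T2 only, so it is a worst case.

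**3. Item-level simulation, closer to the planned group-by-time model.** There were 400,000 simulated participants per scenario. Only the 25 items come from the article. Assumed: don't know scores 0, a correct answer scores 1.6 on average, the chance of don't know falls as latent knowledge rises, and participants are flagged at 10, 13 or 18 don't-know answers at T1 or T2.

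| Latent effect | Cut-off | Excluded, intervention / control | Difference in change, all → retained | T2 difference, all → retained |
|---|---|---|---|---|
| 0.3 | 10 | 37.4% / 41.8% | 2.15 → 1.94 (−10%) | 2.16 → 1.53 (−29%) |
| 0.5 | 10 | 35.5% / 41.9% | 3.53 → 3.16 (−10%) | 3.56 → 2.58 (−28%) |
| 0.8 | 10 | 33.6% / 41.9% | 5.56 → 4.98 (−10%) | 5.60 → 4.23 (−24%) |
| 0.5 | 13 | 17.3% / 21.8% | 3.57 → 3.45 (−3%) | 3.55 → 3.00 (−15%) |
| 0.5 | 18 | 3.1% / 4.2% | 3.52 → 3.53 (none) | 3.54 → 3.41 (−4%) |

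- With no true effect, exclusion was equal between arms and all differences stayed within 0.03 points of zero.
- Flagging on prestudy answers only gave balanced exclusion and a difference in change within −3% to +2% of the full-sample value (for example 3.52 → 3.47 at effect 0.5, cut-off 10).

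**4. Ten lessons against one.** Suppose 5% of lesson views are fast-tracked and any one such view flags the person. If views are independent, the intervention arm is flagged at 1 − 0.95^10 = 40% and the control arm at 5%. If fast-tracking is entirely a habit of the person, both arms are flagged at 5%. Table 1 sums to 180–227 assigned minutes for the intervention and 25–30 for the control, at least seven times as much (180/25 = 7.2; 227/30 = 7.6).

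**The case against.** The strongest objection is that nothing in the article says these participants will be left out of any analysis. The paragraph in question reports what happened in run 1, and the stated response is a second cohort from a paid panel. The per-protocol definition may sit in the full protocol or analysis plan, and its absence from an article is no fault. The article also names other adherence measures, lesson completion and email open rates, from which the set could be built. A reader might infer that the planned per-protocol analysis does select on the knowledge outcome. The documents support that only conditionally, and this part of the objection stands.

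Other parts also stand:
- The flagged behaviour is repeated clicking, and Limitations speaks of noncompliant and fraudulent participants, some perhaps drawn by the incentive. A reader might infer that exclusion removes those with most to learn. The article does not show that the flagged people were genuine low-knowledge care partners.
- The word surveys is wider than the DKAS; dementia stage also has a don't-know category.
- The intention-to-treat analysis keeps everyone, knowledge is a secondary outcome, and the article says the study was not powered to fully assess effectiveness.
- The −30% and the 40% against 5% are worst cases, not expectations.
- The article does not say whether the correlation uses the T2 score or the change, so it cannot be asserted that baseline knowledge drives it.

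What does not fall is the classification itself. Survey answers alone suffice for the label, and the answer concerned is a legitimate one on an effectiveness outcome.

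**Conclusion.** The point holds in conditional form. The article counts a valid, low-knowledge DKAS answer as a sign of not following the protocol. If that description defines the per-protocol set, its poststudy part conditions on the knowledge outcome after randomization.

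The direction is toward no effect, so this mechanism would hide benefit and not create it. The size depends on a cut-off that the article does not give. On the difference in change, which is closest to the planned model, it runs from none at a strict cut-off to about −10% at a loose one. On a T2-only comparison it reaches about −30%. It vanishes with no true effect and is negligible with prestudy flagging only, which changes whom the result describes but leaves the arms comparable. All of this rests on the assumptions listed in the check.

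The imbalance from ten lessons against one may lie anywhere from nil to large, depending on how fast-tracking clusters within people. The matter deserves correction because it costs little, but it does not threaten the primary feasibility aim or the intention-to-treat result.

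**What to change.** 1. State that per-protocol status does not depend on DKAS answers or on answers to any other outcome scale. A screen for uniform answers on the self-efficacy or burden scales would repeat the problem, since those are outcomes too.
2. Keep don't know as a scored DKAS response.
3. Define adherence from platform data: time on content as a fraction of assigned minutes, and survey completion time. The article already lists time to complete the intervention and surveys among its feasibility measures. Set the thresholds while the analysis is still blinded, apply the same rule in both arms and not lesson by lesson, and report the number excluded per arm. A common fraction removes the ten-to-one count of chances, though the intervention arm still has far more minutes to complete.
4. Separately, replace the unadjusted correlation with the association between lessons completed and T2 DKAS, adjusted for the T1 DKAS already collected, and label it as association only.

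The cost is analysis wording; no new data are needed. The small downside is that some careless responders stay in the per-protocol set.

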### Second Cohort Participants

Recruitment for the second cohort began on June 12, 2023, and concluded on June 27, 2023. A total of 100 participants were randomly assigned to either the intervention (n=53) or control group (n=47) group; data collection concluded in September 2023 (Figure 3).

**Figure 3 figure3:**
[figure not shown]
Study flow diagram for run 2.

### Future Results

Results from run 2 of the RCT will be analyzed in spring 2025, published in peer-reviewed journals in the field of aging and geriatrics, and presented at relevant conferences in fall 2025. Results will report on the overall feasibility of implementation of iGeriCare e-learning components in a clinical trial context; care partner acceptance of the intervention (including study methods and participant process); as well as any changes in knowledge, self-efficacy, and burden.

## Discussion

### Overview

The primary objective of this pilot study is to evaluate the feasibility of implementing the iGeriCare e-learning content within a clinical trial context; the secondary objectives include evaluating the feasibility of the study methods and the effectiveness of the intervention. The results of this pilot feasibility study will contribute to the planning of a larger RCT in the future. The iGeriCare RCT has several strengths. First, because the study intervention is freely available on the web, it would be easy to implement, scale, and spread as part of a broader knowledge translation strategy. Second, the intervention is also available in both English and French, which is important for broader dissemination nationally within Canada. Third, while web-based dementia care partner interventions have been previously shown to be effective, those that incorporate evidence-based principles of multimedia instructional design are likely to prove even more effective.

### Limitations

There are some limitations to this work. First, while Meta advertising proved to be an extremely effective and timely recruitment strategy, we did not anticipate the volume of noncompliant (“fast tracker”) and “fraudster” participants that would be recruited during the initial recruitment phase [37]. It is possible that the participation incentive caused some users to declare that they are dementia care partner in the eligibility screener in order to register for the study. To remedy this, a second cohort of participants was recruited through the use of a reputable paid panel service, AskingCanadians. Future studies will look at redesigning a social media recruitment campaign to discourage noncompliance or fraudulent participants. Second, this trial does not look at the long-term impact of web-based education and potential changes to knowledge, self-efficacy, and burden. Future work could consider incorporating additional time points to assess longer-term impacts. Finally, although AskingCanadians was enabled for recruitment of the second cohort of participants, there is still the potential for selection bias and exclusion of those who are lower income or do not have regular access to technological resources. Future studies may explore the barriers to access and look at providing other avenues to web-based resources for disadvantaged populations.

### Conclusions and Next Steps

The expected outcomes related to feasibility are participant acceptance and engagement with the intervention and the study protocol. We anticipate a trend toward an increase in knowledge and self-efficacy, and a reduction in burden in the intervention group, although the study was not powered to fully assess effectiveness. We expect that the study will have implications for future e-learning research with care partners of people living with dementia.

The results of this study will contribute to the planning of a larger RCT in the future, as well as the evaluation of innovative, cost-effective, and efficient dementia care partner resources that can complement traditional approaches. A final manuscript will be prepared to share all results in fall 2025.

## Appendix

Multimedia Appendix 1 Qualitative interview guide.

Multimedia Appendix 2 Peer review report from the PSI Foundation (Ontario, Canada).

## Abbreviations

API: application programming interface
CFIR: Consolidated Framework for Implementation Research
CONSORT: Consolidated Standards of Reporting Trials
DKAS: Dementia Knowledge Assessment Scale
RCT: randomized controlled trial
RSCSE: Revised Scale for Caregiving Self-Efficacy
ZBI: Zarit Burden Interview
